## Abstract

**Background and objective:**

Endothelial dysfunction is a key driver of cardiovascular complications in individuals with impaired glucose tolerance (IGT), with oxidative stress and inflammation playing pivotal roles in its pathogenesis. Although our previous studies have demonstrated that aerobic exercise (AE) significantly ameliorates IGT-induced endothelial dysfunction, the specific roles of oxidative stress and inflammation in this process remain to be elucidated. Therefore, we designed a randomized controlled trial to investigate the effects of AE on vascular endothelial function in patients with IGT and to further explore the underlying regulatory roles of oxidative stress and inflammation.

**Methods:**

Seventy individuals diagnosed with IGT will be enrolled in this two-arm, parallel-group randomized controlled trial, which utilizes an assessor-blinded design. Participants will be assigned in a 1:1 ratio to either a non-exercise control group or a 12-week supervised AE program, consisting of three weekly sessions at 65%–75% of their maximal heart rate. The primary endpoint will be the change in flow-mediated dilation (FMD) from baseline to week 12. Secondary endpoints will include cardiovascular function, glucose and lipid metabolism, circulating inflammatory and oxidative stress biomarkers, and *ex vivo* functional assays using participant-derived serum, including serum transfer experiments using human umbilical vein endothelial cells (HUVECs) and molecular profiling of endothelial progenitor cells (EPCs) cultured in the presence of the participants’ serum. Recruitment commenced in August 2025 and is currently ongoing.

**Discussion:**

This study aims to investigate the impact of a 12-week moderate-intensity AE intervention on vascular endothelial function, oxidative stress, and inflammation levels in patients with IGT. We hypothesize that, compared with the non-exercise control group, 12 weeks of AE will significantly improve endothelial function and exert both systemic and endothelial-derived antioxidant and anti-inflammatory effects.

**Clinical trial registration:**

https://www.chictr.org.cn/, identifier ChiCTR2500106827.

## Introduction

1

Driven by changes in lifestyle and population aging, the prevalence of chronic metabolic diseases continues to increase, with impaired glucose tolerance (IGT) becoming increasingly common (1). IGT represents a high-risk transitional phase between normal glucose metabolism and type 2 diabetes mellitus (T2DM); it not only signals an elevated risk of developing diabetes but also serves as a potent predictor of cardiovascular disease (CVD) (2, 3). Epidemiological and clinical evidence suggest that vascular damage begins as early as the IGT stage (4, 5). Specifically, vascular endothelial dysfunction is recognized as a critical early event in the pathogenesis and progression of vascular disease. By reducing nitric oxide (NO) bioavailability, impairing vasodilatory responses, and promoting arterial stiffness and vascular remodeling, this dysfunction provides the fundamental pathological basis for adverse cardiovascular outcomes in individuals with IGT (6). Consequently, the targeted improvement of endothelial function constitutes a vital intervention strategy for mitigating cardiovascular risk in this population.

Oxidative stress and inflammation are considered primary drivers of metabolic dysregulation and endothelial dysfunction in patients with IGT (2, 7). Under physiological conditions, the body maintains redox homeostasis by regulating the generation and scavenging of reactive oxygen species (ROS) through endogenous antioxidant systems. However, in the context of IGT, glycemic fluctuations and insulin resistance can induce excessive ROS production, overwhelming endogenous antioxidant defenses, and ultimately leading to oxidative stress, metabolic disturbances, and endothelial dysfunction (8). Previous studies have demonstrated that the administration of antioxidants can improve endothelial function in patients with IGT, further highlighting the significance of antioxidant strategies for this population (9). In addition to oxidative stress, accumulating evidence from cellular and animal models of glucose dysregulation indicates that elevated ROS levels are also closely associated with the activation of inflammatory responses, which further aggravate endothelial injury (10–12). Therefore, strategies aimed at specifically modulating oxidative stress and inflammatory processes may represent an important approach for improving endothelial function in individuals with metabolic disorders, including IGT.

It is well established that aerobic exercise (AE) is a cornerstone of IGT management, promoting metabolic and cardiovascular health through various endogenous protective mechanisms. Our previous clinical and preclinical studies have demonstrated that AE ameliorates IGT-related vascular endothelial dysfunction by regulating the eNOS–NO signaling axis (13, 14). However, because of the practical challenges in directly obtaining vascular endothelial tissue from patients in a clinical setting, empirical evidence regarding whether AE-mediated endothelial improvement is linked to the regulation of oxidative stress and inflammation remains scarce. Two experimental paradigms—the use of exercise-conditioned serum and the *in vitro* analysis of endothelial progenitor cells (EPCs)—have provided feasible approaches to addressing this issue. These methods have been successfully employed in cardiovascular disease populations to explore the potential molecular mechanisms by which exercise interventions improve endothelial function (15, 16). Building on these experimental techniques, the present study aims to integrate exercise-conditioned serum experiments with *in vitro* EPC analysis. We will treat human umbilical vein endothelial cells (HUVECs) with serum collected from IGT patients before and after the intervention, while EPCs will be isolated and cultured from peripheral whole blood obtained from the same participants at the corresponding time points. This strategy will allow for a systematic evaluation of oxidative stress and inflammatory responses in endothelial cells, thereby exploring the potential mechanisms by which AE improves endothelial function in individuals with IGT.

We hypothesize that a 12-week moderate-intensity AE intervention will significantly improve vascular endothelial function in patients with IGT. Furthermore, AE may exert both circulating and endothelial-derived antioxidant and anti-inflammatory effects.

## Materials and methods

2

### Research design

2.1

This study will adopt a single-site, assessor-blinded, two-arm parallel controlled trial (RCT) design. Following screening, eligible patients with IGT will be randomly allocated to either the aerobic exercise (AE) group or the control (CON) group in a 1:1 ratio. Participants in the AE group will complete 12 weeks of supervised AE sessions (three times per week), whereas those in the CON group will be required to maintain their habitual lifestyle. Outcome assessments will be performed at baseline and at week 12 (post-intervention); the comprehensive schedule of enrollment, interventions, and assessments is detailed in **Table 1**. The study protocol has received ethical approval from the Ethics Committee of Fujian Normal University (No. 2025-5-30) and was registered with the Chinese Clinical Trial Registry (Identifier: ChiCTR2500106827). All participants will be required to sign a written consent form prior to enrollment. This trial will be reported in accordance with the Consolidated Standards of Reporting Trials (CONSORT) guidelines.

**Table 1 T1:** Participant timeline: schedule of enrollment, interventions, and assessments.

Trial period:	Enrollment		Post-randomization	Close-out
Timepoint	Screening (day-14 to 0)	Baseline (day0)	Intervention period (weeks 1-12)	Week 12 (± 3 days)
Enrollment:				
Eligibility screen	X			
Informed consent	X			
Medical history	X			
Randomization		X		
Interventions:				
Aerobic Exercise Group				
Control Group				
Assessments:				
Primary outcomes				
Flow-mediated Dilation		X		X
Secondary outcomes				
Cardiovascular Function		X		X
Glucose and Lipid Metabolism		X		X
Circulating Biomarkers of Inflammation and Oxidative Stress		X		X
Human Umbilical Vein Endothelial Cells Serum Transfer Experiment		X		X
Endothelial Progenitor Cells Related Molecular Indicators		X		X
Safety monitoring				
Adverse Events		X		X

### Research setting

2.2

This study will be conducted in Fuzhou, Fujian Province. The research team will collaborate with community health service centers and clinics to recruit 70 patients with IGT through strategies including posting recruitment flyers, distributing promotional materials, and conducting health education lectures. All potential participants will undergo initial screening by community physicians, followed by further evaluation and confirmation by endocrinologists from tertiary hospitals and clinical exercise physiologists according to standardized inclusion and exclusion criteria. The exercise intervention will be implemented at exercise rehabilitation centers located within community health service centers, whereas clinical and functional assessments will be conducted at laboratories in partner hospitals and universities. To ensure rigorous adherence to the study protocol, specific roles and responsibilities have been assigned within the research team. Blinded researchers not involved in the recruitment process will be responsible for collecting baseline and post-intervention data. Clinical exercise physiologists not involved in recruitment or clinical assessment will conduct and supervise the exercise sessions. Recruitment was initiated in August 2025 and is currently ongoing (see **Figure 1**).

**Figure 1 f1:**
[figure not shown]
Flowchart of study procedures.

### Inclusion criteria

2.3

Participants must meet all of the following criteria: (1) diagnosis of IGT, specifically defined as: a 2-h postload plasma glucose (2-h PG) level ≥ 7.8 mmol/L and < 11.1 mmol/L as confirmed by a 75-g oral glucose tolerance test (OGTT), with a fasting plasma glucose (FPG) level < 7.0 mmol/L (17); (2) age between 45 and 65 years; (3) identified as a “low physical activity level” via the International Physical Activity Questionnaire (IPAQ), with no regular exercise history; (4) normal cognitive function and the physical capacity necessary to complete the exercise intervention and clinical assessments; and (5) voluntary participation in the study with signed written informed consent.

### Exclusion criteria

2.4

Candidates will be excluded from the trial if any of the following conditions are present: (1) diagnosis of severe cardiac disease, pulmonary dysfunction, or other medical conditions constituting contraindications to exercise; (2) confirmed musculoskeletal disorders resulting in mobility impairment; (3) cognitive or consciousness impairments; (4) current participation in other organized physical activity programs or formal sports training; and (5) diagnosis of T2DM or other metabolic diseases.

### Sample size calculation

2.5

The sample size estimation for this study is based on the primary outcome, flow-mediated dilation (FMD). According to a previous systematic review and meta-analysis regarding the effects of exercise interventions on FMD in patients with T2DM (which included 10 randomized controlled trials and reported a mean FMD improvement of 1.77%, 95% CI: 0.94%–2.59%), the expected intergroup difference (δ) was set at 1.77% with a pooled standard deviation (σ) of 2.2% (18). In the absence of effect size estimates specifically derived from individuals with IGT, data from patients with T2DM were used as a reference. Previous studies have indicated that exercise-induced improvements in endothelial function may be attenuated in patients with T2DM compared to non-diabetic individuals (18). Therefore, using effect sizes derived from T2DM populations is considered a conservative assumption, which is unlikely to overestimate the intervention effect. Sample size calculation was performed using PASS software (NCSS, LLC, Kaysville, Utah, USA). Using a two-independent-sample t-test with a two-sided significance level (α) of 0.05 and a target statistical power (
1−β) of 85%, the results indicated that 28 participants per group were required, totaling 56 participants. At this sample size, the actual statistical power to detect intergroup differences is 85%. Accounting for a potential dropout rate of 20%, we determined a total sample size of 70 participants. These participants will be randomly allocated to the two groups in a 1:1 ratio, with 35 participants recruited per group.

### Random assignment and blinding

2.6

Eligible participants will be randomly assigned to either the AE group or the CON group in a 1:1 ratio. An independent researcher not involved in recruitment or data collection will generate the randomization sequence using Microsoft Excel. To ensure strict allocation concealment, group assignments will be placed in sequentially numbered, opaque, sealed envelopes (SNOSE), which will be maintained by a designated research assistant. To determine group assignment, the envelopes will be opened according to the order of enrollment only after participants have completed all baseline assessments.

This study utilizes an assessor-blinded randomized controlled design. Upon enrollment, participants will be assigned a unique identification code to ensure de-identified data management. All outcome measures, including anthropometric, imaging, and laboratory parameters, will be evaluated by blinded independent researchers. These assessors will remain unaware of both group assignments and specific measurement time points; furthermore, they will be strictly prohibited from communicating with participants regarding intervention experiences or grouping details. Similarly, independent statisticians will analyze de-identified datasets. Throughout the study, only the Data and Safety Monitoring Board (DSMB) and the interventionists (clinical exercise physiologists) will have access to group allocation data. All assessors and statisticians will remain strictly blinded until the final analysis is completed.

### Dietary and medication control

2.7

To minimize potential confounding effects of diet and medication on metabolic, inflammatory, and oxidative stress biomarkers, stringent standardized controls will be implemented across the intervention period. Subjects will be instructed to preserve their habitual dietary patterns and will be prohibited from independently initiating any new dietary interventions, such as caloric restriction or specialized dietary regimens. Furthermore, participants will be required to limit alcohol consumption and maintain a consistent daily caffeine intake. At baseline, all medications and supplements that may influence glucose and lipid metabolism, inflammation, or oxidative stress—including hypoglycemic agents, lipid-lowering drugs, anti-inflammatory agents, and antioxidants—will be comprehensively documented. Subjects will be required to adhere to their existing medication regimens for the duration of the study. The use of any new medications or nutritional supplements will be prohibited unless prescribed by a physician. Any pharmacological changes during the study, including adjustments to medication type or dosage, will be accurately recorded.

### Intervention

2.8

The intervention protocol for this study was developed with reference to the American College of Sports Medicine (ACSM) guidelines for prescribing exercise to T2DM populations (19). All supervised sessions will be scheduled 1–2 hours postprandially to manage exercise-related glucose fluctuations. Given that the acute enhancement of insulin sensitivity following a single exercise bout typically persists for only 24–72 hours, the interval between consecutive sessions will be maintained at no more than 48 hours to ensure cumulative metabolic benefits and prevent the attenuation of intervention effects (19, 20). The AE intervention will follow the FITT principles (frequency, intensity, time, type) and will be managed by exercise physiologists. The intervention period will span 12 weeks, with three supervised sessions per week. Each session will consist of a 5-minute preparatory warm-up (50%–60% of HR_max_), 50 minutes of aerobic exercise (65%–75% of HR_max_), and a 5-minute cool-down (50%–60% of HR_max_). The HR_max_ will be calculated using the Tanaka formula: HR_max_

=208−0.7×age. Participants will utilize heart rate monitors (Polar Electro, Kempele, Finland) for instantaneous intensity observation to ensure exercise intensity remains within the target range. For participants exhibiting chronotropic incompetence (blunted heart rate response) or those receiving heart rate-modulating medications (e.g., non-dihydropyridine calcium channel blockers or β-blockers), exercise intensity will be prescribed using a combination of the Borg Rating of Perceived Exertion (target range 12–14) and heart rate. The control (CON) group will receive no structured exercise intervention and will receive clear directions to maintain their habitual lifestyle. During the intervention period, researchers will assess the physical activity levels of the CON group every two weeks using the International Physical Activity Questionnaire (IPAQ). Participants in the intervention group will also be instructed not to engage in any additional structured exercise beyond the prescribed training program during the study period to ensure consistency of the intervention dose. Considering the minimum effective dose required for exercise-induced benefits, participants who complete less than 75% of the prescribed training sessions will be considered non-adherent in the per-protocol analysis.

### Safety considerations and adverse event monitoring

2.9

Before each training session, a mandatory health evaluation will be performed to screen for symptoms including excessive fatigue, palpitations, and dizziness. We will perform finger-prick glucose tests exclusively on participants showing signs of acute dysregulation (e.g., diaphoresis, tremors, or lightheadedness) or general malaise. The exercise intervention will be postponed if blood glucose levels meet any of the following criteria: > 16.7 mmol/L; < 3.9 mmol/L; or > 13.9 mmol/L accompanied by symptoms of metabolic decompensation or ketonuria.

In accordance with ACSM standards, sessions will be terminated immediately upon detecting angina-like symptoms; a decrease in systolic blood pressure (SBP) > 10 mmHg despite an increase in intensity; or an exaggerated hypertensive response (diastolic blood pressure [DBP] >115 mmHg or SBP > 250 mmHg); signs of poor perfusion, dizziness, or severe shortness of breath; and pronounced ST-segment changes or clinically significant arrhythmias. All adverse events—including cardiovascular symptoms, musculoskeletal injuries, and any unexpected reactions—will be formally recorded by the supervising exercise physiologist in a standardized Case Report Form (CRF). These records will be independently adjudicated by a DSMB, which will evaluate the severity and causality of the events to the intervention to decide on the necessity of trial modifications.

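### Adverse-event recording is tied to a role and to sessions that only the exercise arm has, so harms cannot be compared between arms without ascertainment bias

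*Protocol article*

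**What the plan says.** Section 2.9 sets a wide scope, "All adverse events—including cardiovascular symptoms, musculoskeletal injuries, and any unexpected reactions", and names one recorder: events "will be formally recorded by the supervising exercise physiologist in a standardized Case Report Form (CRF". The same section describes active symptom enquiry: "Before each training session, a mandatory health evaluation will be performed to screen for symptoms including excessive fatigue, palpitations, and dizziness". The monitoring board then judges severity and causality from these records and decides whether the trial needs changing.

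Section 2.2 defines the recorder's role: "Clinical exercise physiologists not involved in recruitment or clinical assessment will conduct and supervise the exercise sessions". Section 2.8 gives the AE arm its sessions ("The intervention period will span 12 weeks, with three supervised sessions per week") and gives controls none: "The control (CON) group will receive no structured exercise intervention and will receive clear directions to maintain their habitual lifestyle". The one regular control contact stated for weeks 1 to 12 has another purpose: "researchers will assess the physical activity levels of the CON group every two weeks using the International Physical Activity Questionnaire (IPAQ".

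Table 1 in section 2.1 has a row "Adverse Events" under safety monitoring. It is marked at baseline and at week 12, not restricted by arm, and shows no mark in the column for weeks 1 to 12.

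**The concern.** The plan gives recording of all events, not only those during exercise, to a person whom controls never meet in that capacity. It also places the only active symptom screen at visits that controls do not attend. No other recorder is named for control-arm events.

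Unequal enquiry of this kind tends to produce unequal counts even when the true risks are the same. Minor complaints that arise in any middle-aged group would be noted in the AE arm and largely missed in controls. The monitoring board would then judge whether exercise caused an event without a usable background rate, and the final report could show an excess in the AE arm that comes from how often people were asked. Recruitment is under way (section 2.2), and control-arm events not asked about now are hard to recover later.

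**Working it through.** The plan states no adverse-event figure, so there is none to reproduce. The check is a count of opportunities by arm, followed by an illustration.

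**Opportunities for an event to be recorded after randomization**

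| | AE | CON |
|---|---|---|
| Supervised sessions with symptom screening (2.8, 2.9) | 3 × 12 = 36 | 0 |
| Two-weekly questionnaire contacts (2.8) | none stated | 12 / 2 = 6, physical activity only |
| Week-12 mark (Table 1) | 1 | 1, if the mark covers both arms |
| Named recorder (2.9) | supervising physiologist | none |

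The baseline mark does not help. Section 2.6 opens the allocation envelopes only after all baseline assessments, so that mark comes before randomization.

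**Who could carry out the week-12 enquiry in controls?** Section 2.2 keeps the physiologists out of clinical assessment. The outcome assessors are blinded, and section 2.6 bars them from discussing intervention experiences or grouping with participants. The text therefore identifies nobody clearly placed to ask.

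**What unequal capture does.** Let the true risk p be equal in both arms, and let c be the share of events captured in each arm.

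- Apparent risk ratio = (p × c_AE) / (p × c_CON) = c_AE / c_CON.
- Apparent risk difference = p × (c_AE − c_CON).

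The document gives neither p nor c, so the values below are assumptions: c_AE = 1, p = 20%, and 35 participants per arm (section 2.5).

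| c_CON | Expected events, AE | Expected events, CON | Apparent risk ratio |
|---|---|---|---|
| 100% | 35 × 0.20 = 7.0 | 7.0 | 1.0 |
| 75% | 7.0 | 5.25 | 1.33 |
| 50% | 7.0 | 3.5 | 2.0 |
| 25% | 7.0 | 1.75 | 4.0 |

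With c_CON between 25% and 75% and p between 10% and 40%, the spurious risk difference runs from 0.10 × 0.25 = 2.5 to 0.40 × 0.75 = 30 percentage points. These figures show the mechanism and are not an estimate for this trial. Only equal capture gives a ratio of 1.

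**Primary outcome.** FMD is measured by blinded assessors at the same two visits in both arms, and adverse-event records do not enter the mixed model in section 2.14. The primary inference is untouched.

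**The case against.** The strongest reply is that the plan promises no between-arm safety comparison. Adverse events are neither a primary nor a secondary outcome, section 2.14 specifies no safety test, and section 2.9 is mainly about keeping sessions safe. That is correct, and it limits the point to descriptive reporting of harms and to the monitoring board's causality judgement. It does not remove the point, because that judgement is the stated use of the records.

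Three stronger readings are tempting, and the document does not support them.

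- *That the arms cannot be compared on safety at all.* The week-12 mark in Table 1 is not limited by arm, so a crude comparison from one common enquiry remains possible. Section 2.7 also has medication changes recorded with no arm restriction, which is a partial route for medically significant events.
- *That Table 1 contradicts section 2.9.* The two intervention rows of the table are also blank in the text available, so graphic marks for weeks 1 to 12 may have been lost. Even if that cell really is empty, scheduled enquiries at two visits can coexist with recording events as they occur. The two places need aligning; a contradiction is not shown.
- *That the imbalance is 36 contacts against 1.* That sets sessions against a table mark. Counted as contacts, controls have about six plus week 12; what they lack is a stated adverse-event question at those six.

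It can also be said that a condensed article leaves control-arm procedures to the full protocol, and that closer watching of a supervised arm is unavoidable. The first would answer mere silence, but here the article assigns all events to a one-arm role. The second is true of session-triggered events, and is the reason to list them separately.

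**Conclusion.** The point holds as a matter of ascertainment. Following the plan as written, AE participants are screened for symptoms at up to 36 sessions by the sole named recorder. Controls have about six contacts with no stated adverse-event enquiry and at most one enquiry at week 12. Event counts therefore cannot be compared between arms, or set against a control background rate by the monitoring board, without ascertainment bias. If capture is lower in controls, which is the likely direction, exercise will look more harmful than it is.

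The size of the bias cannot be derived from the document; the ratios of 1.33 to 4.0 above rest wholly on assumed capture rates. The conclusion rests on reading section 2.9 literally, as covering all events in the trial, and does not depend on the blank cell in Table 1. The FMD result is not affected. The change is worth making because it is cheap and recruitment is in progress.

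**What to change.** - Ask the same short adverse-event checklist every two weeks in both arms: in CON at the existing questionnaire contact, by staff who are not the blinded outcome assessors; in AE at one of that fortnight's sessions.
- State in section 2.9 who records control-arm events.
- Base any between-arm description of harms on this common collection, and list events noted only because of a session separately.
- Align the adverse-event row of Table 1 with section 2.9, including what happens in weeks 1 to 12 and whether the week-12 mark covers both arms.

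The cost is a few minutes at contacts that already take place and one line on the case report form. It needs no new visits or staff, and no clinical rule changes.
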